##### Sensitivity analysis

In the sensitivity analyses, we will impute missing values of the outcomes and covariates using MICE. Furthermore, we will compare the results of the primary analysis with the results for different subgroups to assess the stability of the results.

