**Methods:**

The Value-based TKR study is a prospective pragmatic multi-center, stepped wedge, cluster randomized controlled trial (SW-RCT). The EKIT tool provides (1) a systematic presentation of individual patient and disease-specific information (symptoms, expectations), (2) the fulfillment of the indication criteria and (3) health information about safety and effectiveness of TKR. All study sites will follow routine care as control clusters until the start of the intervention. In total, there will be 10 clusters (study sites) and 6 sequential steps over 16 month, with clusters receiving the intervention with a minimum 2 months of standard routine care. The primary outcome is patients’ decision quality measured with the Decision Quality Instrument (DQI)-Knee Osteoarthritis questionnaire. Furthermore, we will collect information on global patient satisfaction, patient reported outcome measures and the fulfilment of the individual expectations 12 months after SDM. The power calculation yielded an estimated power of 89% using robust Poisson regression under the following assumptions: 10 study sites with a total of N=1,080 patients (including a dropout rate of 11%), a 10% increase in decision quality due to the use of the EKIT tool, and a significance level of 5%.

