### Study design

The Value-based TKR study is a prospective pragmatic multi-center, stepped wedge, cluster randomized controlled trial (SW-RCT). Each cluster will be randomly assigned to interventions on a staged schedule. In total, there will be 10 clusters (study sites) which will change from control (routine care) to the intervention (EKIT tool) in a predefined randomly allocated sequence. Each cluster will have a minimum 2 months of routine care before changing to the intervention (Fig. 1). At the end of the study, all clusters will be assigned to the intervention with a minimum of 4 months. The total duration of study will be 16 months.

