#### Statistical power

The power calculation was based on the primary study outcome (decision quality). A rather conservative scenario to estimate the expected power of the confirmatory analysis was chosen. The calculation was performed for a stepped wedge cluster randomized trials design with a recruitment period of 16 months. Based on a previous study on the effectiveness of a decision aid for patients with osteoarthritis [50], the baseline probability of ‘good decision quality’ measured by DQI-Knee Osteoarthritis [48] was assumed to be 44.5%. Furthermore, we assumed a 10 % increase in decision quality by the implementation of the EKIT tool as decision aid.

We expected 10 participating study sites with an average number of 108 enrolled patients per site over the entire time period (N total = 1,080), accounting for an estimated dropout rate of 11%. The intervention (EKIT tool) was assumed to be implemented sequentially as described in Fig. 1. The modeling of possible correlations within the clusters was performed as part of the data generation process using a logistic multilevel model with a standard deviation of the random intercept of 0.01. Based on these assumptions and a significance level of 5%, the assumed intervention effect on decision quality can be estimated using robust Poisson regression with a power of 89%. The power calculation was performed with the statistical software R [51].

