#### Statistical methods

All analyses will be evaluated by intention-to-treat principles in terms of assignment to treatment and use a level of significance of 0.05. Study sites, which stop participation after the trial start date or will not implement intervention, will be included in the analysis. There are no interim-analyses planned for this study. We will use the statistical software R [51] for all analyses.

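### Comparing subgroup results with the overall result does not test whether the effect differs; interaction terms in the planned Poisson model would

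*Protocol article*

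**What the plan says.** The Sensitivity analysis section of the protocol article has two parts. The first is multiple imputation of missing outcomes and covariates. The second is the subgroup check: "we will compare the results of the primary analysis with the results for different subgroups to assess the stability of the results". The section does not name the subgroups or say whether p-values, estimates or intervals are to be compared. No section mentions an interaction term.

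Three other places bear on the point:
- Statistical methods states that all analyses "use a level of significance of 0.05".
- Confirmatory analysis specifies a complete-case robust Poisson regression for clustered data. It notes that the regression gives a direct estimate of the relative increase in good decision quality, and that covariates can be added in sensitivity analyses.
- Statistical power gives power for the whole sample only: the effect "can be estimated using robust Poisson regression with a power of 89" per cent.

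**The concern.** The article fixes both a comparison (subgroup against whole sample) and a purpose (judging stability), and the comparison does not serve the purpose. The whole-sample estimate is a weighted average that includes the subgroup, so the two are correlated by construction. The contrast that carries information about consistency is subgroup against complement. The subgroup is also smaller, so its result scatters more widely and reaches significance less often even when the effect is the same everywhere.

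There is also a question of label. Imputing missing data varies an assumption behind the same estimate, which is what a sensitivity analysis does. Asking whether the effect differs by patient or site characteristic is a different, exploratory question.

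At stake is how robustness is described in the report. A uniform effect might be called unstable, or a chance difference might be presented as a group that responds and a group that does not.

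**Working it through.** **Inputs.** From Statistical power: control probability "was assumed to be 44.5" per cent; effect "we assumed a 10 % increase in decision quality by the implementation of the EKIT tool as decision aid"; sample size "N total = 1,080), accounting for an estimated dropout rate of 11" per cent. From the abstract: "there will be 10 clusters (study sites) and 6 sequential steps over 16 month". From Study design: "Each cluster will have a minimum 2 months of routine care before changing to the intervention", and at least 4 months of intervention.

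**Assumptions.** Two-sided alpha; switches at months 2, 4, ..., 12 with 1, 2, 2, 2, 2, 1 sites; even recruitment. Control share = (1×2 + 2×4 + 2×6 + 2×8 + 2×10 + 1×12)/(10×16) = 70/160 = 0.4375.

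**Step 1: reproduce the 89%.** Read the 10% as absolute (44.5% to 54.5%; risk ratio 1.22). With N = 1,080 there are 472.5 control and 607.5 intervention patients.
- SE(log RR) = √[0.555/(0.445×472.5) + 0.455/(0.545×607.5)] = 0.0634
- log(0.545/0.445) = 0.2027
- Power = Φ(0.2027/0.0634 − 1.96) = 0.892

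With N = 961 (1,080 × 0.89) the same formula gives 0.855. A simulation of the stepped wedge without period terms gives 0.899 to 0.906 for N = 1,080 and 0.869 to 0.882 for N = 961. The stated figure is reproduced. The relative reading (44.5% to 48.95%) gives only about 0.28 to 0.31.

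**Step 2: subgroups read by significance, uniform effect, two equal halves.**
- Non-centrality for 89% power: 1.96 + 1.2265 = 3.1865
- In each half: 3.1865/√2 = 2.253
- Power per half: Φ(2.253 − 1.96) = 0.615
- At least one half non-significant: 1 − 0.615² = 0.62
- Exactly one half significant: 2 × 0.615 × 0.385 = 0.47
- Given a significant overall result: two significant halves in the same direction imply a significant whole, so 1 − 0.615²/0.89 = 0.57

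Working from the two sample sizes instead of the stated 89%, the 62% becomes 60% (N = 1,080) to 66% (N = 961). A 20/80 split gives 75% to 78%. Three or five independent equal splits give 78% or 84% (simulated).

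**Step 3: estimates or intervals compared instead.** Let a subgroup be a fraction f of the sample and σ the SE of the overall estimate. The subgroup-minus-overall difference has SD σ√(1/f − 1).

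| f | Subgroup estimate outside overall 95% CI: 2Φ(−1.96/√(1/f − 1)) | Overall estimate outside subgroup 95% CI: 2Φ(−1.96/√(1 − f)) |
|---|---|---|
| 0.50 | 5% | 0.6% |
| 0.25 | 26% | 2.4% |
| 0.20 | 33% | 2.8% |

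For any of 3 to 5 independent equal splits, the middle column becomes 14% to 23%. The same sentence of the article thus covers false-alarm rates from about 1% to 33%, or about 60% and above if significance is the yardstick.

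**Step 4: the interaction term.**
- With a uniform effect, false alarms are 5% per factor (simulated 0.050 to 0.053 without period terms).
- Unadjusted over several independent factors: 1 − 0.95³ = 14%; 1 − 0.95⁵ = 23%.
- Power for 15 versus 5 points in equal halves, on the difference scale: SE = 0.0645 (N = 961) or 0.0609 (N = 1,080), so Φ(0.10/SE − 1.96) = 0.34 or 0.38.
- On the ratio scale, which the Poisson model uses, the same alternative is log(0.595/0.495) = 0.184 with SE 0.135 or 0.127, so power is slightly lower, 0.28 or 0.30.
- 20 versus 0 points on the difference scale: 0.88 to 0.91.

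**The case against.** The strongest objection is that the article commits itself to very little. It compares results without a p-value rule, a threshold or a consequence. The Confirmatory analysis section describes the primary result as an estimated relative increase, so comparing estimates is at least as natural a reading as comparing significance. Interaction terms are not excluded, and the detail may stand in an analysis plan that is not shown. Repeating an analysis in a restricted population is also a recognised stability check. Statistical methods keeps sites that stop or never implement the tool, and a repeat without them would be legitimate and could not be replaced by an interaction term.

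Much of this stands. A reader might infer that the check will signal instability most of the time. That holds only if instability means loss of significance in some subgroup, a criterion the article does not state. A reader might also infer that a faulty comparison would distort the trial's conclusion or the decision on roll-out. The article ties neither to this check: the confirmatory conclusion comes from the single primary analysis. Nor do the documents support replacing the whole subgroup sentence, because they do not say which kind of subgroup is meant.

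What does not stand is that an analysis plan listing the subgroups would settle the matter. The stated contrast, subgroup against a whole that contains it, would still not test a difference in effect.

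**Conclusion.** The point holds as a low-severity, cheap improvement. The stated comparison does not test whether the effect differs and has no defined error rate. Read by significance, it would leave at least one of two equal halves non-significant in about 62% of trials under a uniform effect (57% of those with a significant overall result). Read by estimates or intervals, false alarms run from about 1% to 33%, depending on subgroup size, number of factors and which interval is used.

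These figures rest on the stated 89% power, two-sided testing, normal approximations, and assumed subgroup sizes and numbers of factors. The structural criticism depends on none of them.

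**What to change.** For patient or site characteristics fixed before the consultation (t0), assess consistency with treatment-by-subgroup interaction terms in the primary robust Poisson model:
- Keep the list short and specify it in advance.
- Report the ratio of risk ratios and the subgroup risk ratios, each with a 95% confidence interval.
- State that consistency is not judged by significance within subgroups.
- Place this under Explorative analysis.

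Re-analyses in restricted populations, for example without sites that did not implement the tool, can remain under Sensitivity analysis.

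The cost is a change of wording and a few model terms; no data collection changes. The downside is low power for moderate differences (about 0.34 to 0.38 for 15 versus 5 points on the difference scale, somewhat less on the ratio scale) and unadjusted false positives of 14% to 23% over 3 to 5 factors. The interactions should therefore be read as estimates with intervals, not as pass-or-fail tests.

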##### Explorative analysis

The statistical analysis of the secondary outcome parameters is exploratory-hypothesis generating. In addition to descriptive standard methods, multilevel models will be used to explore potential factors influencing the outcome parameters. Multiple Imputation by Chained Equations (MICE) will be used for the imputation of missing data in the explorative analysis. In addition, we plan to investigate the cohort with regard to epidemiological questions for influencing factors that have a predictive impact on outcomes 12 months after surgery. Furthermore, we will explore the adherence to the clinical guideline.

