### Study aims

The purpose of this study is (1) to compare the effectiveness of the EKIT tool versus routine care in terms of decision quality and satisfaction with the SDM. Furthermore, we aim to (2) investigate with a 12-month follow-up the impact of the EKIT tool on treatment choices, patient reported outcomes measures (PROM) and satisfaction with treatment outcome. (3) We aim to investigate associations that influence the decision quality on patient and intervention level. Specific study hypotheses are:
*Hypothesis 1*: Patients receiving the intervention have higher decision quality than patients receiving routine care.*Hypothesis 2*.1: Patients report higher satisfaction with the SDM when the EKIT tool was used.*Hypothesis 2*.2: Physicians report higher satisfaction with the SDM when the EKIT tool was used.*Hypothesis 3.1:* After 12 months, patients are more satisfied with their chosen therapy if the EKIT tool was used.*Hypothesis 3.2:* After 12 months, patients are more satisfied with the treatment decision made if the EKIT tool was used.*Hypothesis 3.3:* After 12 months, individual patient expectations are more likely fulfilled if the EKIT tool was used.

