##### Patient inclusion criteria for SW-RCT

The target population includes all patients with knee osteoarthritis which are referred for TKR by the treating physician. Eligibility criteria are: (1) patient with knee osteoarthritis who is a candidate for total knee replacement, (2) capacity to consent, (3) understanding of the German language (written and oral), (4) age of 18 years or older, and (5) informed consent. Patients with already performed knee replacement ipsilateral will be excluded from the study.

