##### Secondary outcomes

Patient and physician satisfaction measured on a 5-point Likert-scale with the SDM will be analyzed regarding intervention effects. Furthermore, we will collect the following secondary outcomes 12 month after SDM: patients satisfaction with (1) their chosen therapy measured by the global treatment outcome (GTO) [44] and (2) treatment decision measured by the Decision Regret Scale (DRS) [49] to determine if there is exploratory evidence of differences between intervention and control. We will further investigate the fulfilment of the individual expectation between the groups measured on a 5-point Likert-scale, 12 months after SDM. Details on secondary outcome parameters, measurement instruments and time frames are listed in Table 1.

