##### Participant timeline

The participant timeline contains the enrollment, two digital assessments (t_0_, t_2_) and the follow-up (t_3_) 12 months after consultation (Fig. 2). The data collected at the various time points are shown in Table 1.

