##### Follow-Up (t3)

The follow-up will take place 12 months after SDM. Study staff will contact all patients by mail to fill in a questionnaire including current global health status, disease-specific complaints, degree of fulfillment of preoperative expectations, patient satisfaction with the treatment outcome and satisfaction with decision-making and global treatment outcome.

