### Data collection, management, and analysis

#### Data collection methods and data management

Overall, the majority of data will be collected electronically, with the exception of the follow-up survey. Figure 2 summarizes the data collection process in this study. A web application platform for collection of the data was developed for this study. This web application includes the questionnaires in both phases and additionally the EKIT tool in the intervention phase. Each questionnaire is checked by the web application, ensuring valid answers for all required questions. All data protection issues are detailed in a separate data protection concept.

The follow-up questionnaire (t_3_) will be sent by mail 12 months after t_1_. After four weeks without a response, study staff will send a reminder for the follow-up survey (t_3_). Patients will receive no kinds of incentives or compensation for participation in this study.

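### An exploratory predictor analysis is tied to 12 months after surgery, but the only follow-up is timed from the consultation

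*Protocol article*

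**What the plan says.** The Explorative analysis section of the protocol article adds an epidemiological question to the trial comparisons: it will look for "influencing factors that have a predictive impact on outcomes 12 months after surgery".

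The sections that set the timing of the follow-up use a different starting point, and they agree with one another:

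- Participant timeline: "two digital assessments (t_0_, t_2_) and the follow-up (t_3_) 12 months after consultation".
- Follow-Up (t3): "The follow-up will take place 12 months after SDM".
- Secondary outcomes: "we will collect the following secondary outcomes 12 month after SDM".
- Data collection methods and data management: "The follow-up questionnaire (t_3_) will be sent by mail 12 months after t_1", where t1 is the consultation visit.
- Primary outcome: the treatment received is also reported at this follow-up, 12 months after the consultation.

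Table 1 has one follow-up column (t3), and its close-out column holds no assessment. Nothing in the article is timed from surgery.

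**The concern.** The sentence in Explorative analysis names a time point that the trial does not observe. A reader of the results would take them to describe recovery at one year after knee replacement, whereas the operated patients will generally be at an earlier stage, and probably not all at the same one.

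For a predictor analysis this is more than a labelling matter. Time since surgery at t3 depends on how long each patient waited. If a baseline factor such as study site or disease severity goes with a shorter wait, patients with that factor have had longer to recover when they answer. The factor can then appear to predict a better outcome when part or all of the association is recovery time.

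**Working it through.** The article states no figure for this point, so there is none to reproduce. The check sets the sections side by side and adds one subtraction.

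**Step 1: order of events.** Patient inclusion criteria state: "Patients with already performed knee replacement ipsilateral will be excluded from the study". The index knee therefore has no replacement at entry, and any study TKR follows the consultation by some wait W.

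**Step 2: who has a time since surgery.** Primary outcome distinguishes conservative treatment from TKR. Conservatively treated patients have no surgery date, so the planned time point does not exist for them. The same holds for anyone still waiting at t3.

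**Step 3: time since surgery at t3.** The form is mailed 12 months after t1, so for an operated patient

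months since surgery at mailing = 12 − W.

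A reminder goes out after four weeks without a response. A form returned about one month late is answered at 13 − W.

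**Step 4: numbers.** W is not given in the article. The values below are assumptions for illustration.

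| Assumed wait W (months) | Months since surgery at mailing (12 − W) | If returned one month later (13 − W) |
|---|---|---|
| 0.5 | 11.5 | 12.5 |
| 1 | 11 | 12 |
| 2 | 10 | 11 |
| 3 | 9 | 10 |
| 4 | 8 | 9 |
| 6 | 6 | 7 |
| 9 | 3 | 4 |

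**Step 5: reading the table.** At mailing, every operated patient with W above zero is short of 12 months. The spread in time since surgery equals the spread in W: waits of 1 to 6 months give 11 − 6 = 5 months between the shortest and the longest wait. A patient with a short wait who answers after the reminder can be at or slightly past 12 months, so the shortfall is general but not universal.

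**The case against.** The strongest reply is that this is one loosely worded clause. Every section that sets the follow-up agrees on the consultation, the clause belongs to an analysis declared exploratory, and predictors of outcome after surgery are not among the listed study aims or hypotheses. This stands, and it limits the weight of the point. It does not remove it: an analysis carried out and reported as written would carry a wrong time label, and its associations would be open to the recovery-time explanation.

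Some stronger readings are tempting, but the documents do not support them:

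- *A main aim cannot be answered.* The third aim in Study aims concerns influences on decision quality. The predictor question is a supplementary one.
- *The 12-month comparisons in hypotheses 3.1 to 3.3 are biased.* Study aims promises to "investigate with a 12-month follow-up the impact of the EKIT tool on treatment choices", and these hypotheses concern the chosen therapy, the decision made and the fulfilment of expectations. The consultation is the one starting point that operated and conservatively treated patients share, and it fits analysis by assigned phase. If the tool changes when patients are operated on, that is part of its effect.
- *Waiting times drift over the 16 months and so separate control from intervention patients.* The article says nothing about such a drift. Methodological considerations already acknowledges secular trends as a general risk of the design.
- *The date of surgery is not collected, so the interval cannot be recovered.* Table 1 lists no such date, but it is a summary table in an article. It also has no separate row for the treatment received, which Primary outcome says is collected. Its silence does not show that the date is missing, and a site's operation record could supply it.

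**Conclusion.** The inconsistency is certain: one sentence promises outcomes at 12 months after surgery, and the only follow-up is 12 months after the consultation. That operated patients are earlier in recovery when the form is sent follows from the order of events. That they differ from one another rests on waits differing between patients, which is plausible across ten sites but cannot be sized from the article; the 1 to 6 month range is an assumption. Confounding of a predictor by recovery time is therefore a possibility to guard against, not a demonstrated bias.

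Severity is minor. The confirmatory analysis, the primary outcome, the power calculation and the comparisons under hypotheses 3.1 to 3.3 are unaffected and need no change.

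**What to change.** 1. In Explorative analysis, reword the sentence so that it refers to outcomes 12 months after the consultation, in line with the sections that set the follow-up.
2. If it is not already captured, record the date of TKR, or that the patient has not yet been operated on, either as one item on the mailed t3 questionnaire or from the site's operation record.
3. Restrict the models for predictors of post-surgical outcome to operated patients and include months since surgery as a covariate, counted to the date the form is answered so that late returns are handled correctly. Make no claim about a fixed 12 months after surgery.

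The cost is one data item and a slightly less ambitious exploratory claim. No visit or patient is added.
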